### 2.11. Anthropometric Measurements and Body Composition

Weight and height will be self-reported by adults. For the children, measures will be taken by the survey staff using the same scales and stadiometers in the three survey centres (KaWe Height Measure, KaWe Kirchner & Wilhelm, and Seca 880 Weight Scale, Seca Ltd., for height and weight measurements, respectively). Body mass index (BMI) will be calculated as weight (kilograms)/height (square meters). Body composition in adults will be determined with the supplied wearable band. In children, it will be estimated by dual-energy x-ray absorptiometry (Hologic QDR series Discovery W densitometer, Hologic, Bedford, MA, USA).

### 2.12. Blood Pressure and Heart Rate

For adults, the wristband will measure blood pressure and heart rate. For children, blood pressure will be measured using oscillometric measurement with automated blood pressure and pulsometer.

### 2.13. Stool Samples

Stool sample containers will be provided to the participants and will be collected at T0, T1, and T2. The following measurements will be performed: fecal microbiota profiles, targeted metabolomic profiles (SCFAs and bile acids).

### 2.14. Urine Samples

Urine sample containers will be provided to the participants and will be collected at T0. Targeted analysis of specific metabolites will be performed to detect potential metabolic pathologies [16,17].

### 2.15. Blood Samples

Blood samples will be collected only in children at T0 and T2. The following biochemical parameters will be measured in blood samples: total protein, albumin, lipid profile, urea, creatinine, alanine and aspartate aminotransferase, alkaline phosphatase, electrolytes, ferritin, serum calcium, and vitamin D.

### 2.16. Storage of Biological Specimens

Biological samples will be stored under appropriate conditions and used exclusively for research purposes upon the consent of the donor.

### 2.17. Data Management

Data will be recorded on electronic datasheets and kept in an anonymous form. Sensitive data will be kept entirely separate from other data under lock and key and accessible only to key research team members. A 5-digit participant-ID code will be assigned to each subject included in the study. The ID code will be built as follows: the first digit denotes the country of residence, the second digit denotes children or adults, the last three digits denote the subject. Each document or item related to each subject will be labelled with the respective ID code.

Specific strategies will be employed to improve data quality during data collection, including accurate recruitment, a structured protocol, the inclusion of a run-in period, the use of standardized procedures, and the possibility to complete questionnaires online.

### 2.18. Statistical Analysis

The primary outcome (alpha diversity) will be analysed within each group using paired comparison t-tests to evaluate whether the changes from baseline to 12 weeks will be statistically significant. The absolute change (value at baseline subtracted from value after intervention for each subject) will be estimated with independent t sample tests. ANOVA will be used to analyse taxonomic diversity data and to assess the association of the GM composition with the phenotypic characteristics of the study population. Sensitivity analyses will be undertaken based on the assumption that missing outcomes are the worst possible, or the best possible, in different randomization groups. A significance value *p* < 0.05 will be considered statistically significant. Alpha diversity calculations and statistical analyses will be performed using various packages in the R platform, including the Vegan library (v2.5-2; Oksanen et al., 2012).

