### 2.3. Intervention Study and Mobile App i-Diet Stance4Health

This study will be a multicentre (five recruiting centres), parallel group randomised controlled trial, characterised by the use of the nutritional software mobile app i-Diet Stance4Health (Figure 1). A statistical model was developed to predict nutrients that must be incorporated into the diet of participants to transform their gut microbiota back into a healthy state, close to that of normal weight subjects. Based on the statistical model, the i-Diet Stance4Health app will suggest food choices in retailers and give participants specific advice about nutrition and lifestyle (taking into account or not GM composition, respectively for treated or control groups). The app will generate personalised diets (breakfast, lunch, dinner, snacks) based on Mediterranean dietary patterns encouraging fruits, vegetables, and whole grains consumption which are foods rich in compounds that have been shown to have positive effects on GM composition [15]. Tannins pills will supplement the diet since they have proven effective in modifying GM composition and functionality [16]. Participants’ health status, objectives, and habits (desired daily intakes, dishes that make up these intakes) will also be considered. The i-Diet Stance4Health will be used as a novel tool to record food intake (dietary assessment). To do so, participants, or parents in the case of children, will learn how to use the app through specific instruction/training. Specifically, they will indicate which serving size they usually prefer by pointing to it in the set of photographs to facilitate the estimation of the portion size. The users will also have the opportunity to make variations in the proposed menu. The app will estimate menus taking into account the nutritional values of foods and recipes by using a food composition database specifically developed in the framework of the Stance4Health project [17]. After a 2-week run-in period, the eligible participants will be randomly assigned to a 12-week intervention with two different levels of personalised nutrition: Level 1 and Level 2.

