### 2.5. Outcome Measures

Variation in GM alpha diversity, which will characterise species diversity change in each individual due to the impact of the intervention, represents the primary end point [22,23]. This end point is determined by 16S rRNA gene-targeted sequencing of microbial DNA isolated from stool samples. For selected samples, shotgun metagenomic and meta-transcriptomic sequencing will be applied.

Besides the changes in GM composition, consumer empowerment through technology adoption and long-lasting adoption of a healthy and sustainable diet are additional relevant outcomes of the intervention study.

The study comprises a number of secondary outcomes including appetite regulation and food intake, anthropometry (body weight, waist circumference, and body composition), blood pressure, physical activity levels, short-chain fatty acids and bile acids in feces, and urine metabolomics.

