### 2.6. Sample Size and Power Calculation

The sample size was determined to detect an anticipated change in GM alpha diversity of 25% from baseline between control and treated groups. Based on a previously published trial conducted to test the efficacy of personalized nutrition intervention on alpha diversity [24,25], in the case of healthy adult subjects a sample size of at least 200 in each intervention level, totalling 400 individuals, will allow us to obtain a statistical power of 80% (beta) and alpha = 0.05. In case of loss to follow-up, extra volunteers will be enrolled to compensate. Due to the lack of specific data for children, the above calculations were extrapolated to the children’s group.

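### Section 2.18 gives the primary outcome to within-arm paired t-tests and plans a between-group test of change beside them without fixing which groups it compares or that it decides efficacy

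*Protocol article*

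**What the plan says.** Section 2.5 makes the change in gut microbiota alpha diversity the primary endpoint and describes it as the change in the individual that the intervention brings about.

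Section 2.18 gives two analyses for it.

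- The first is within-arm: "The primary outcome (alpha diversity) will be analysed within each group using paired comparison t-tests". Its stated purpose is to judge the significance of the 12-week change in each arm.
- The second takes each participant's absolute change, which "will be estimated with independent t sample tests". The sentence does not name the groups compared and gives the test no precedence.

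One threshold, p < 0.05, covers all tests.

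Section 2.6 sets the sample size to "detect an anticipated change in GM alpha diversity of 25% from baseline between control and treated groups", which is a between-arm contrast. Section 2.3 has both arms use the same app, whose advice draws on microbiota composition in the treated arm and not in the control arm. Of the diet itself it says: "The app will generate personalised diets (breakfast, lunch, dinner, snacks) based on Mediterranean dietary patterns". Section 2.3 also adds tannins or placebo in Level 2 only.

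**The concern.** A paired t-test inside one arm asks whether alpha diversity at 12 weeks differs from baseline in that arm. It is an uncontrolled before-after comparison. Anything that moves both arms together, above all the common app diet, counts as a positive result in the treated arm.

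Finding significance in treated but not in control does not repair this, because it is not a test of the difference between the arms.

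The primary outcome is tied by name to this test, and no sentence makes the between-group test decisive. With two levels and two arms in each, an independent-samples test could mean treated against control or Level 1 against Level 2. An analyst who follows section 2.18 literally could report the treated arm's change as the primary result when the arms do not differ. A placebo-controlled randomised trial would then draw its main conclusion from a comparison that ignores the control arm.

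**Working it through.** **1. The plan's own figure.** Section 2.6 asks for 200 adults per level and says that this number "will allow us to obtain a statistical power of 80% (beta) and alpha = 0.05". Section 2.3 divides each level equally, so there are 100 treated and 100 control. No SD or baseline mean is given, so the number can be neither reproduced nor refuted. Solving backwards (two-sided 0.05, normal approximation):

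- standardised difference = (1.960 + 0.842) × √(2/100) = 0.396;
- implied SD of change for a 25% difference = 25 / 0.396 ≈ 63% of baseline.

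This calculation belongs to a treated-versus-control comparison, as section 2.6 says. If the paired test were the one powered, n = 100 would instead imply an SD of 25 / (2.802 / √100) ≈ 89% of baseline. The two analyses in section 2.18 are therefore not interchangeable for power.

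**2. Inputs for the error check.**

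- n = 100 per arm (sections 2.6 and 2.3).
- Two-sided 0.05. The article states 0.05; two-sided is assumed.
- True mean change equal in both arms, d SDs of the change score. The values of d are assumptions.

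**3. Formulas.** With noncentrality d√n, 99 degrees of freedom and critical value t = 1.984:

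- U = P(treated arm shows a significant increase) = 1 − F(1.984), where F is the noncentral t distribution function;
- p = P(an arm is significant in either direction);
- P(treated significantly up, control not significant) = U × (1 − p).

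For d = 0.2 the noncentrality is 0.2 × 10 = 2, U = 0.508, and 0.508 × 0.492 = 0.250. For d = 0.3 it is 3, U = 0.844, and 0.844 × 0.156 = 0.132.

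**4. Results with no treated-control difference.**

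| Shared shift d | Treated arm significantly up (paired) | Treated up, control not significant | Between-arm t-test significant (simulated) |
|---|---|---|---|
| 0 | 2.5% | 2% | 5.2% |
| 0.1 | 17% | 14% | not run |
| 0.2 | 51% | 25% | 4.8% |
| 0.3 | 84% | 13% | 4.7% |
| 0.4 | 98% | 2% | not run |

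The last column comes from 20,000 simulated trials per row. In the same simulations, a significant increase in the treated arm occurred together with a non-significant between-arm test in 48% of trials at d = 0.2 and 82% at d = 0.3.

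**5. Why a shared shift is plausible.** Section 2.3 gives both arms app-generated diets built on foods that it describes as acting favourably on the microbiota. Section 2.10 describes reminders, tips and periodic feedback for participants without separating the arms. The control arm is thus an active intervention, and some change in it is to be expected.

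**The case against.** The strongest reply is that the between-arm test is already there. Independent-samples t-tests on change scores can only compare groups. Section 2.6 names treated versus control, section 2.1 calls the trial randomised and placebo-controlled, and the missing-data sensitivity analysis in section 2.18 is set out by randomisation group. All of this points to an intended treated-versus-control comparison. Ranking of tests is also often left to an analysis plan, which is not shown here.

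Much of this stands, and it rules out several stronger readings.

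- A reader might infer that the paired test is the only test of the primary outcome. The next sentence of section 2.18 shows that it is not.
- A reader might infer that the plan counts a within-arm change as efficacy. No sentence says so. The risk is what the text permits, not a stated decision rule.
- A reader might take 51% and 84% as the type I error of the paired test. They are its power against its own null of no change over time, and become false-positive rates only if that test is used to claim efficacy.
- A reader might count every trial in which exactly one arm is significant (50% at d = 0.2, 26% at d = 0.3). Half of these are control-only results, which nobody would report as efficacy. The relevant figures are 25% and 13%.
- A reader might add regression to the mean or the run-in as causes. The eligibility criteria in section 2.2 do not select on alpha diversity. The run-in precedes randomisation, and Table 1 puts allocation and the first stool sample at Day 0. Neither is well supported.

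What the reply does not remove is the explicit sentence that assigns the primary outcome to within-group significance tests. That is a stated analysis and not a detail left out. An analysis plan that follows it inherits the problem; one that does not will depart from the published protocol.

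**Conclusion.** The concern holds in this form: within-arm significance tests stand as a primary analysis beside a between-group test whose compared groups and deciding role are not fixed. The within-arm tests do not answer the randomised question and do not match the contrast that was powered.

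If a within-arm result were used as evidence of efficacy, a shared shift of 0.2 to 0.3 SD would give a positive treated arm 51% to 84% of the time with no true difference. The pattern of treated significant and control not would occur 25% to 13% of the time. The between-arm test would keep its error near 5%.

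These figures rest on 100 per arm, two-sided 0.05, normally distributed changes with equal SDs, and shift sizes that the article does not supply. The direction of the conclusion does not depend on the exact shift, since any shared increase raises the treated arm's rejection rate and leaves the between-arm test unaffected.

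**What to change.** In section 2.18, and in the analysis plan if there is one:

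1. Name the treated-versus-control comparison of the 12-week change in alpha diversity, within each intervention level, as the confirmatory analysis of the primary outcome.
2. Present within-arm changes as descriptive means with 95% CIs.
3. State that no efficacy claim rests on a within-arm change.

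This costs wording only. No extra data or participants are needed, and the sample size stands as framed because section 2.6 already describes it as a treated-versus-control comparison. The change should be made before the allocation sequence is released for analysis. It does not settle how multiple levels and child populations are handled, which is a separate question.

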### 2.4. Participants Timeline

Each intervention period will last 3 months. At the first contact, information about potential participants’ age, sex, anthropometry, dietary habits, health status, and contact details will be collected to select people with the inclusion/exclusion criteria identified for each study population. For this purpose, people will be encouraged to fill in specific questionnaires and return them by hand, by email, or online. Eligible participants will be asked to fill out the informed consent plus a number of questionnaires on their lifestyle, bowel, and dietary habits. Data will be collected using paper or, due to the epidemiological situation produced by the COVID-19 pandemic, online questionnaires [20]. In the latter case, participants will receive a link to open and accept the informed consent and to proceed with the completion of the questionnaires. On the Stance4Health webpage (www.stance4health.com, accessed on 18 March 2022), three different links (buttons) for the different languages (Spanish, German, and Greek) are included to allow participants to fill out the questionnaires online.

Three clinical evaluations of the study populations will be performed: at the beginning (T0), after 6 weeks (T1), and at the end of the interventions (T2) (Table 1). At T0 and T2, health [(blood pressure, previous pathologies, anthropometric (height, weight, waist circumference, fat mass, muscle mass)], dietary (food frequency questionnaires—FFQ), lifestyle (smoking habits, physical activity and sleep patterns), and socioeconomic status information will be collected in specific datasheets. Two FFQs will be used in the study, the FFQ_IDEFICS/i.Family [21] and the FFQ_S4H specifically developed for the study of GM. GM composition and metabolomic profile, and SCFAs and bile acids levels in feces will be assessed three times: at T0, T1, and T2.

At the end of the intervention, participants will have the opportunity to continue using the technologies for free as an incentive not to withdraw from the study. Moreover, all participants can choose to use the full functionality of i-Diet Stance4Health and associated elements (such as GM analysis and the food supplements), even if they were included in the control group. This could be an indicator of the acceptability and utility of the intervention.

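### The between-arm test of alpha diversity is a valid but unadjusted t-test on change; adjusting for baseline would gain precision at no extra data, and the worst/best-case missing-data rule needs a usable form

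*Protocol article*

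**What the plan says.** Section 2.5 makes the change in gut microbiota alpha diversity the primary endpoint. Section 2.18 names two analyses for it:

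- within each group, "paired comparison t-tests to evaluate whether the changes from baseline to 12 weeks will be statistically significant";
- between groups, "The absolute change (value at baseline subtracted from value after intervention for each subject) will be estimated with independent t sample tests".

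No covariate is attached to either. The ANOVA in the same section is for taxonomic diversity and for associations with phenotype, not for an adjusted treatment comparison.

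For missing outcomes, Section 2.18 states: "Sensitivity analyses will be undertaken based on the assumption that missing outcomes are the worst possible, or the best possible, in different randomization groups". It does not say what value counts as worst or best.

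The primary outcome is measured three times. Section 2.13 says "Stool sample containers will be provided to the participants and will be collected at T0, T1, and T2", and Sections 2.4 and 2.18 place these at baseline, week 6 and week 12. On size, Section 2.6 says "The sample size was determined to detect an anticipated change in GM alpha diversity of 25% from baseline between control and treated groups", with at least 200 per intervention level, 80% power and alpha 0.05. Section 2.3 divides each level equally into control and treated, so adults have 100 per arm per level. Adults come from two countries. Children come from three Greek centres and four clinical populations.

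**The concern.** A change-score t-test implicitly fixes the coefficient of baseline at 1. When the correlation between baseline and follow-up is below 1, that coefficient is too large. The test then carries avoidable noise, and chance baseline imbalance is over-corrected. Estimating the coefficient removes that noise. Every input is already collected, so the precision is lost without any saving. Country, centre and child population are also plausible sources of variation in diversity that the named test leaves in the error term.

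The second matter is the sensitivity analysis. A binary outcome has an obvious worst and best value, but a continuous diversity index does not. As written, the analyst must choose the values, and the width of the bounds depends on that choice. If the bounds are very wide at ordinary dropout, the analysis cannot help a reader judge whether missing stool samples threaten the result.

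**Working it through.** **Plan's own figure.** Section 2.6 gives no SD, diversity index, baseline mean or correlation, so the 200 per level cannot be reproduced. It can only be solved backwards. With 100 per arm, two-sided 0.05 (sidedness is assumed) and 80% power, the detectable standardised difference is

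d = (1.960 + 0.842) × √(2/100) = 0.396 SD of change.

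A 25% difference then implies an SD of change of 25/0.396 ≈ 63% of baseline. This back-solved 0.396 is the anchor below. It is not a figure from the article.

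**Baseline adjustment.** Let σ² be the common variance at baseline and week 12, and rho their correlation.

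- Variance per participant, change score: 2(1 − rho)σ²
- Variance per participant, analysis of covariance: (1 − rho²)σ²
- Ratio: (1 − rho²) / [2(1 − rho)] = (1 + rho)/2

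Power with adjustment is Φ(0.396/√ratio × √50 − 1.960).

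| rho (assumed) | Variance ratio | Power at 100 per arm | Per arm for 80% |
|---|---|---|---|
| none (change-score t-test) | 1 | 80% | 100 |
| 0.3 | 0.65 | 93.5% | 66 |
| 0.5 | 0.75 | 89.9% | 75 |
| 0.7 | 0.85 | 86.0% | 85 |
| 0.9 | 0.95 | 82.0% | 95 |

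A simulation of 3,000 runs agrees in direction and size: from 79.9% to 89.3% at rho 0.5, and from 78.3% to 84.2% at rho 0.7. Below rho 0.5 the change score is noisier than the week-12 value alone, with a variance ratio of 2(1 − 0.3) = 1.4 at rho 0.3.

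**Country or centre.** If these terms explain 2% to 10% of the variance (assumed), 80% power becomes 81% to 84%.

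**Children.** 400 / (4 populations × 2 levels × 2 arms) = 25 per arm in each population and level. For the same standardised difference, power is 28.8% with the t-test and 30% to 41% with adjustment (rho 0.9 to 0.3). Adjustment helps but does not rescue comparisons of that size.

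**Week 6.** Under equal correlations of 0.5 to 0.7, using the week-6 value reduces the variance of the week-12 contrast by 0% with no missing data, about 1% to 2% with 10% missing and 2% to 3% with 20% missing.

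**Extreme-case rule.** With a fraction m missing in each arm and extremes at ±k SD, the estimate runs from (1 − m)d − 2mk to (1 − m)d + 2mk. At m = 0.10 and k = 2 (both assumed) this is 0.357 ± 0.400, that is −0.04 to +0.76 SD.

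Using the pooled observed minimum and maximum instead (normal data, 100 per arm, 4,000 runs) gives:

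- True difference 0.40 SD, 10% missing: estimates average −0.19 (worst case) to +0.91 SD (best case). The worst case is significant in favour of treatment in essentially 0% of runs, and significant against it in about 11%.
- No true difference, 10% missing: the best case is significant in favour of treatment in about 91% to 92% of runs.
- True difference 0.40 SD, 2% missing: the worst case stays significantly favourable in about 43% of runs.
- True difference 0.80 SD, 5% missing: it stays significantly favourable in about 83%.

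**The case against.** The strongest reply is that the planned test is unbiased under randomisation and keeps its type I error, so this is only a matter of efficiency. That is correct. It is also fair that a separate analysis plan, not shown, may add covariates, an analysis set or a missing-data model. The point therefore rests on the test and the rule that Section 2.18 does state, not on what it leaves out. The extreme-case analysis is a declared sensitivity analysis and deliberately conservative, and bounding can be applied to continuous outcomes once the extremes are defined. That also stands, and is why this part is secondary.

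Several stronger readings are tempting but unsupported:

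- A reader might infer that baseline is ignored. It is subtracted for each participant; what is missing is its use as a covariate.
- A reader might infer a completers-only analysis. A change score needs both values, but no analysis set is named, and the sensitivity analysis addresses missing outcomes by randomised group.
- A reader might say that randomisation strata are left out of the model. Section 2.7 names no stratification factors. What is left out is the known country, centre and population structure.
- A reader might take "In case of loss to follow-up, extra volunteers will be enrolled to compensate" to mean that volunteers take dropouts' places. Section 2.6 does not say so, and newly randomised additional participants would fit the text.
- A reader might conclude that leaving out week 6 costs much precision. The calculation shows at most about 3% of variance.
- A reader might conclude that the worst case overturns any realistic result. It does not at low dropout or with larger effects.

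**Conclusion.** The concern holds as one of efficiency, with a smaller one about the sensitivity analysis. The unadjusted change-score t-test is valid, but it gives up between 5% (rho 0.9) and 35% (rho 0.3) of the variance reduction available from a baseline measurement already in hand. In power this is a rise from 80% to between 82% and 94%. The range rests on an assumed correlation, equal variances at the two times, and the article's claim of 80% power taken at face value for 100 per arm. At high correlation the gain is small; in large samples it is not negative.

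The extreme-case rule is undefined for this outcome as written. With observed extremes it is close to uninformative at about 10% missing per arm, and less so at low dropout or with larger effects. The article states no dropout rate, so 10% is an assumption.

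**What to change.** Before unblinding, replace the between-group t-test with an analysis of covariance of week-12 alpha diversity on treatment, baseline alpha diversity and country or centre, comparing treated with control. Add child population as a term where the children's groups are pooled. The unadjusted change-score test can stay as a supporting analysis.

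Replace or supplement the worst/best-possible rule with multiple imputation, which may use the week-6 value, followed by a tipping-point analysis that shifts imputed values by stepwise deltas until the conclusion changes. If the extreme-case analysis is kept, state what value counts as worst and best.

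The cost is a revision of Section 2.18 or the analysis plan, one degree of freedom per added parameter, and a little more programming. No new data, visits or samples are needed.

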### 2.2. Eligibility Criteria

Five study populations will be included in the study:(1)Apparently healthy adult subjects (both sexes), aged 20–65 years, with a body mass index (BMI) between 20–28 kg/m^2^, stable weight, ability to use a smartphone, and Internet connection availability. Exclusion criteria are the diagnosis of chronic gastrointestinal (GI) disorders, coeliac disease, or chronic diseases such as diabetes or other metabolic diseases; present pregnancy or lactation (<6 weeks before study start), or intention to become pregnant in the next 12 weeks; recent inflammation and/or long-term use of an-ti-inflammatory drugs; medically prescribed diet or specific dietary regimens for any reasons (i.e., high-protein diet, vegetarianism, veganism, etc.); antibiotic treatment (<3 months before study start); intake of antioxidant, pre- or probiotic supplements (<1 month before study start); intense physical activity (>10 h/week); alcohol consumption >21 drinks/week for men and >14 drinks/week for women.(2)Normal weight children (of both sexes), aged 6–11 years, with a BMI >5th and <85th percentile for age, gender, and height. Exclusion criteria are the diagnosis of chronic GI disorders and any other chronic disease, elimination diet, intake of probiotics (<2 weeks before study start).(3)Children (of both sexes) with obesity, aged 6–11 years, with a BMI ≥95th percentile for age, gender, and height. Exclusion criteria are the diagnosis of chronic GI disorders and endocrinopathies, intake of probiotics (<2 weeks before study start).(4)Children (of both sexes) with gluten-related disorders, aged 6–11 years, diagnosed with coeliac disease or wheat allergy (sIgE), on elimination diet. The exclusion criteria are the absence of symptoms.(5)Children (of both sexes) with allergy/intolerance to cow’s milk, aged 6–11 years, with an IgE-mediated milk allergy on an elimination diet from infancy, lactose intolerance (symptoms plus breath hydrogen positive test), overgrown IgE-mediated milk allergy but current aversion for milk, or nondefinable phenotype (children who avoid milk but do not belong to any of the previous phenotypes). Exclusion criteria are the diagnosis of other GI comorbidities.

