Level 1 (entry-level) intervention will consist in the use of i-Diet Stance4Health and the analysis of GM and metabolites. Level 2 (advanced level) will consist of the use of i-Diet Stance4Health and the analysis of GM and metabolites (as in the entry level), plus the use of a wearable wrist band only in adults, a metabolomics test to check the presence of metabolism disorders [18,19], and the intake of tannins extracts in pills for adults and in biscuits for children (treated group) or placebo (control group). The wearable band will be used to record physical activity, heart rate, blood pressure, and body composition as well as to refine food intake. Tannin extracts will be produced and distributed looking for a deeper modulation of the GM [16]. All data recorded in i-Diet Stance4Health and by the wearable band and results of the analyses will be recorded in specific databases. In detail, 200 Spanish and German adults will follow the entry-level intervention, and 200 will follow the advanced level intervention, equally divided into control and treated groups. The same criteria will be used for 400 Greek children (100 normal weight, 100 with obesity, 100 with gluten-related disorders, and 100 with allergy/intolerance to cow’s milk). Among them, half will be included in Level 1 and half in the Level 2 intervention.

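### The primary outcome is tested at a flat 0.05 in up to ten treated-versus-control cells, by two kinds of t-test, and none is named as deciding efficacy

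*Protocol article*

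**What the plan says.** - **Populations (section 2.2).** "Five study populations will be included in the study": one adult population and four of children.
- **Levels and arms (section 2.3).** In the adult part, "200 Spanish and German adults will follow the entry-level intervention, and 200 will follow the advanced level intervention", and these are "equally divided" in substance: "200 will follow the advanced level intervention, equally divided into control and treated groups". The same scheme is applied to 400 children, 100 in each of four groups, half of them in each level.
- **Endpoint (section 2.5).** There is one primary endpoint, variation in gut microbiota alpha diversity.
- **Sizing (section 2.6).** The target is "an anticipated change in GM alpha diversity of 25% from baseline between control and treated groups". The adult requirement is given as "a sample size of at least 200 in each intervention level, totalling 400 individuals". The article gives the design values as 80% power and a significance level of 0.05. The calculation is then carried over to children.
- **Analysis (section 2.18).** Paired t-tests are run within each group from baseline to 12 weeks, and independent-samples t-tests are applied to the absolute change. ANOVA is used for other questions. For all of them, p below "0.05 will be considered statistically significant".
- **Question to be answered (Introduction and Results).** The trial is presented as a test of whether one service is effective.

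No section ranks the populations or levels, says whether child groups are pooled, or says whether the paired or the independent t-test carries the efficacy conclusion.

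**The concern.** A single efficacy question is put to many tests of the same outcome at the same threshold, with no rule for turning the results into an answer. Followed as written, any one significant cell could be reported as the trial's efficacy finding.

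The two kinds of test make this worse. A paired test inside one arm is not a randomised comparison. Under section 2.3 the control arm also receives app-generated Mediterranean-style diets, without use of microbiota data. Alpha diversity could therefore change in both arms with no difference between them, and a significant paired result in a treated arm would say nothing about the treatment contrast.

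The child cells are small. With an equal split each arm has 25 children, so an isolated significant cell there would be weak evidence.

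**Working it through.** **1. The plan's own figure.** The sample size cannot be reproduced because section 2.6 gives no standard deviation. It can be inverted. With 100 per arm within a level, two-sided 0.05 and 80% power, the detectable standardised difference is (1.960 + 0.842) × √(2/100) = 0.396. For a 25% difference this implies an SD of 25/0.396 ≈ 63%. The sizing is thus a treated-versus-control test inside each adult level at the full 0.05, which already makes two primary tests.

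**2. Number of comparisons.** 5 populations × 2 levels = 10 treated-versus-control cells, and 10 × 2 = 20 arms. Arm sizes are 200/2 = 100 for adults and 100/2/2 = 25 for children, assuming an equal split in children.

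**3. Chance of at least one false positive if there is no effect anywhere.** The cells contain different participants, so the between-arm tests are independent and the chance is 1 − (1 − α)^m. For either direction α = 0.05. For results favouring treatment only, α = 0.025.

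| Family of treated-versus-control tests | m | Either direction | Favouring treatment only |
|---|---|---|---|
| Two adult levels | 2 | 1 − 0.95² = 9.75% | 1 − 0.975² = 4.9% |
| Adults and pooled children, by level | 4 | 1 − 0.95⁴ = 18.5% | 1 − 0.975⁴ = 9.6% |
| Every population by level | 10 | 1 − 0.95¹⁰ = 40.1% | 1 − 0.975¹⁰ = 22.4% |

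**4. If within-arm tests also counted as evidence of efficacy.** Twenty paired tests give 1 − 0.95²⁰ = 64.2%. All 30 t-tests (20 paired, 10 independent) give about 70% by simulation under no change in any arm, allowing for the correlation between tests in the same cell. Treating the 30 as independent would give 78.5%, which is too high.

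**5. What the remedies cost in power**, at the design difference of 0.396 with 100 per arm:

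- Bonferroni over the two adult tests (0.025 each): power falls from 80% to 71%, and about 122 per arm would restore it.
- Bonferroni over all ten (0.005 each): power falls to 50%, and about 170 per arm would be needed.
- Fixed order at 0.05 each, stopping at the first non-significant result: the first test keeps 80%. If the effect is at its design value in both adult levels, the chance that both succeed is 0.80 × 0.80 = 64%. Family-wise error stays at 5% because a later test is reached only when all earlier ones are significant.

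**The case against.** Much of the structure is fixed: section 2.5 names one endpoint, section 2.6 gives the contrast (treated against control), and section 2.18 gives the time span (baseline to 12 weeks). Separate testing of ten cells is not stated in section 2.18, and section 2.6 speaks of children as one group, which is compatible with pooling. The stated threshold could be applied to adjusted p values. Different disease populations can be seen as separate questions, for which adjustment is debated. Testing order is often left to an analysis plan, and none is shown here.

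These points narrow the concern without removing it. What remains open is the population or level and the type of t-test. Even the narrowest reading, the two adult levels, gives 9.75%. The article also does more than stay silent: it assigns two kinds of test to the primary outcome under one threshold and ranks neither.

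A reader might infer more than this, and the text does not support it:

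- **That a false-positive efficacy claim is likely.** The between-arm figure is at most 40%. It passes 50% only if within-arm tests are counted as efficacy evidence, which the article neither says nor excludes.
- **That the ANOVAs will yield many false taxon findings.** The article says "ANOVA will be used to analyse taxonomic diversity data and to assess the association of the GM composition with the phenotypic characteristics". This does not commit to one test per taxon, gives no number of tests, and does not carry the primary efficacy claim.
- **That samples from T0, T1 and T2 are analysed as if independent.** Nothing says so. The primary analysis uses paired tests and within-person change.

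**Conclusion.** The concern holds for the primary outcome. Endpoint, contrast and time span are set, but no population, level or test is designated as deciding, and every test uses 0.05. The chance of at least one false-positive treated-versus-control result is about 40% for ten cells (22% counting only results favouring treatment), 19% for four comparisons with children pooled, and 9.75% for the two adult levels.

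These figures assume two-sided tests, a single alpha diversity index, no adjustment of p values, and no true effect in any cell. The ten-cell figure also assumes separate testing in each cell. An analysis plan that is not shown may already settle the matter.

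**What to change.** In section 2.18, state that the treated-versus-control comparison of change in alpha diversity from baseline to 12 weeks is the sole basis for any efficacy claim, and that the paired within-arm tests are descriptive.

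Before unblinding, fix a testing order at two-sided 0.05 for each step. Start with the two adult level comparisons, on which the trial is sized, and stop at the first non-significant result. If a formal claim in children is wanted, its place in the order and any pooling must be written down at the same time. Report the remaining population-specific results as estimates with confidence intervals.

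The change is to wording only and needs no additional participants. Its downside is that a comparison later in the order loses its formal claim when an earlier one fails, and results left outside the order carry none. The sponsor should therefore choose which adult level comes first with that in mind. No change to the ANOVA is asked for.
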